### Outcomes

#### Primary outcome

The primary outcome is survival without moderate or severe BPD at PMA 36 weeks, which is defined as the following criteria: no respiratory support, spontaneous breathing FiO_2_ 0.21 for SpO_2_ 92%.

#### Secondary outcomes

Amplitude-integrated electroencephalography (aEEG). A series of aEEGs will be monitored once a week for all preterm infants after 30 weeks PMA. Sleep-wake cycles of aEEG can be classified as absent, mature, or immature according to Hellstrom-Westas [31]. The PMA of mature sleep-wake cycles occurred will be used as one of the neurodevelopmental outcomes and be compared between two groups.Intraventricular hemorrhage (IVH) > grade II and/or periventricular leucomalacia (PVL). A series of cranial ultrasound scans will be performed regularly for all preterm infants, and these results will be extracted from the medical records after enrollment. IVH > grade II and/or PVL will be used as an adverse outcome to be compared between the groups [32].Brain volume at 40 weeks PMA. Total brain volume will be detected by using the functional MRI of the brain Software Library for automatic segmentation of the T1/T2 weighted images. The mean/median total brain volumes will be compared between groups at 40 weeks.Nosocomial infection, including cultured proven sepsis, meningitis, and pneumonia. Culture-proven infection is defined as a positive culture obtained from sputum, urine, blood, or cerebrospinal fluid of infants with clinical signs of infection, and pneumonia will be confirmed by abnormal lung examination (such X-ray, CT).Neonatal necrotizing enterocolitis (NEC). Bell stage II or more and/or focal intestinal perforation diagnosed by X-ray after enrollment to hospital discharge [33].Gastrointestinal bleeding diagnosed by the contents of the digestive tract.Retinopathy of prematurity (ROP). A series of fundus examinations will be arranged after enrollment, and ROP that needs treatment in any stage will be used as an adverse outcome [34].Anthropometric indices. Body length, head circumference, and body weight at 36 weeks of PMA.Hyperglycemia. Hyperglycemia that needs to be treated with insulin (serum glucose levels ≥ 200 mg/dl) after enrollment.Hospitalization days.

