### Participants

Inclusion criteria:
Gestational age 26^+0^ to 30^+6^ weeks and birth weight < 1500 g; andDiagnosed early BPD at day 28, based on NICHD criteria [4] and never received any glucocorticoids after birth; andOne of the following conditions:
Oxygen reduction test showing SpO_2_ < 90% with FiO_2_ > 0.3 orNoninvasive ventilation support or nasal cannula with FiO_2_ > 0.21.

Exclusion criteria included any of the following conditions:
Invasive ventilation support needed on the 28th day of life.Congenital malformations affecting pulmonary function (e.g., congenital surfactant protein deficiencies, congenital diaphragmatic hernia) or increasing the risk of death or adverse neurodevelopmental outcome (e.g., congenital cerebral malformations, congenital hydrocephalus).Chromosomal defects (e.g., trisomy 13, 18, 21).Severe infection less than 7 days before randomization (late-onset sepsis/meningitis confirmed by positive blood culture; bacterial pneumonia, confirmed by positive tracheal culture; neonatal necrotizing enterocolitis).

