### Trial medication and dosing

Trial medication will be prepared and distributed according to Good Clinical Practice (GCP) and Good Manufacturing Practice (GMP) guidelines. Using a double-blinded, placebo-controlled design, infants will be allocated to either HC or placebo treatment.

The long-term adverse neurodevelopmental outcomes observed with dexamethasone use are associated with the accumulative dosage [30]. The optimal (cumulative) dose of HC is currently unknown. In one previous study, Baud et al. [21] found that an early (< 7 days) low dose of HC increased the rate of survival without BPD at 36 weeks PMA without adverse neurodevelopmental outcomes at 2 years of age [22, 24]. Based on these findings, we adopted this dosage in the present study. Infants randomly assigned to the HC group will receive 0.5 mg/kg HC twice per day for 7 days, followed by one dose of 0.5 mg/kg per day for 3 days. This leads to a total duration of therapy of 10 days and a cumulative dose of 8.5 mg/kg HC. The control group will receive an equal volume of saline and will not receive any other intervention on the basis of routine treatment.

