### Randomization

Eligible patients will be randomized at day 28 after birth in each center after at least one guardian provides informed consent. A list of all eligible patients not included in the study will be provided from all centers throughout the time of enrollment. This trial will be protected from selection bias by using concealed, stratified, and blocked randomization. Randomization will be stratified according to gestational age stratum (26^+0^ to 28^+6^ weeks, and 29^+0^ to 30^+6^ weeks) in each study center. Multiple birth infants will be internally randomized. The randomization procedure will be generated by using Excel software by the GCP faculty at the participating hospitals, and it will be sealed in a sequentially numbered envelope to maintain the allocation concealment. According to the allocation sequence, drug packages will be hidden and labeled sequentially. Participants will receive packaged drug in the order of recruitment. The first dose of study medication will be administered within 1 h after randomization.

The complete random sequence will be kept by the primary researcher at the affiliated hospital of Southwest Medical University. Centers will individually have emergency envelopes that contain the treatment information for patients. Emergency envelopes can be unsealed only under special conditions.

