### Clinical data collection

At the time of randomization, baseline data will be collected from all included patients, including maternal and patient characteristics. Demographic data will include sex, birth weight, gestational age, 5-min Apgar score, surfactant therapy, prenatal corticosteroid use, premature rupture of the membrane before the onset of labor (> 18 h), singleton/multiple birth, and mode of delivery. Population characteristics will be used to compare outcomes between the two groups.

The following clinical data will be collected: continuous positive airway pressure (CPAP)-assisted time, invasive ventilator-assisted time, days of hospitalization, days on supplemental oxygen, IVH, spontaneous intestinal perforation, NEC, and ROP.

During HC treatment, respiratory support, blood sugar, blood pressure, and anthropometric data will be collected. Outcome variables and cointerventions will be recorded at 36 weeks PMA.

After discharge, one trained investigator in each center will follow up all patients at 40 weeks PMA and at 12, 26, 52, and 104 weeks corrected age. We will provide free neurodevelopmental impairment examinations to promote follow-up rates. For potential dropouts during the follow-up, we will expand the sample size by 20% and the missing data will be ignored in the analysis. The outcomes at each time point mentioned above will be collected by the investigators (Table 1).

**Table 1 Tab1:** SPIRIT figure: showing time points for enrollment, interventions, and assessment

	Study period						
	Enrollment	Allocation	Post-allocation				Close-out
Time point	At 4 weeks after birth	At 4 weeks after birth	At 36 weeks postmenstrual age	At 40 weeks postmenstrual age	At 12, 26 weeks corrected age	At 52 weeks corrected age	At 104 weeks corrected age
Enrollment:							
Eligibility screen	X						
Informed consent	X						
Demographic data	X						
Allocation		X					
Intervention:							
Hydrocortisone		X					
Placebo		X					
Assessments:							
Baseline variables assessments	X	X					
Primary outcome			X				
Secondary outcomes:							
Brain volume				X			
Others			X				
Long-term outcomes:							
Neurodevelopmental impairment, hearing loss, and blindness							X
Number of readmissions						X	
Weight, length, and head circumference				X	X	X	X
Behavioral problems, premature birth-related mortality							X

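### Some secondary outcome windows are not anchored to day-28 randomization or conflict with each other; the aEEG outcome can be fixed up to 28 days before the first dose

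*Protocol article*

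**What the plan says.** Only the protocol article is at hand; all places below are in it.

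- **Entry and treatment.** Participants: "Gestational age 26^+0^ to 30^+6^ weeks and birth weight < 1500 g". Randomization: "Eligible patients will be randomized at day 28 after birth in each center", and "The first dose of study medication will be administered within 1 h after randomization". Trial medication and dosing: "This leads to a total duration of therapy of 10 days and a cumulative dose of 8.5 mg/kg HC".
- **aEEG.** Secondary outcomes: "A series of aEEGs will be monitored once a week for all preterm infants after 30 weeks PMA". The value compared between arms is the PMA at which mature cycling occurs. No rule covers infants already mature at entry.
- **IVH/PVL, infection, bleeding.** IVH/PVL results come from regular cranial ultrasound and are taken from the records after enrollment. That phrase may date the extraction or the scans. Nosocomial infection and gastrointestinal bleeding have no stated start.
- **Outcomes that are anchored.** NEC is defined as "Bell stage II or more and/or focal intestinal perforation diagnosed by X-ray after enrollment to hospital discharge". ROP examinations and insulin-treated hyperglycemia are dated from enrollment, as is mortality under Long-term outcomes after hospital discharge.
- **End of the window.** Clinical data collection: "Outcome variables and cointerventions will be recorded at 36 weeks PMA". Table 1 puts brain volume at 40 weeks PMA and every other secondary outcome at 36 weeks. Secondary outcomes nevertheless runs NEC to discharge and lists hospitalization days, and Ethical and academic management has adverse effects monitored until discharge.

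**The concern.** An outcome that is settled before the first dose cannot respond to hydrocortisone. Counting it adds infants in whom the two arms differ only by chance, which moves a comparison of PMA at maturity towards no difference. For a neurological safety outcome, that is the direction that hides harm.

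IVH/PVL, infection and bleeding raise the same question more weakly, because their start is unclear rather than clearly before entry. Prior IVH/PVL is not an exclusion. Severe infection is excluded only if it occurred in the 7 days before randomization, so earlier episodes are possible. The baseline list in Clinical data collection contains no cranial imaging.

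At the other end, two readings of the harm window coexist: to 36 weeks PMA, or to discharge. Under the first, follow-up for harm depends strongly on gestational age at birth and is shortest in the most mature infants. The trial's stated aim covers safety as well as efficacy, so the analysed window should not be left to interpretation.

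**Working it through.** **The plan's own figures.** Duration: 7 + 3 = 10 days. Cumulative dose: 7 × 2 × 0.5 + 3 × 0.5 = 8.5 mg/kg. Both agree with Trial medication and dosing.

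**Formulas, in days.** Gestational age (GA) at birth runs from 26+0 (182) to 30+6 (216), which is 35 eligible values.

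- PMA at entry = GA + 28
- aEEG time before entry = PMA at entry − max(210, GA), where 210 is 30+0
- Last dosing day = PMA at entry + 9, since dosing starts within an hour of randomization
- Entry to 36+0 = 252 − PMA at entry

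| Born at | PMA at entry | aEEG days before entry | Last dosing day | Days from entry to 36+0 |
|---|---|---|---|---|
| 26+0 | 30+0 | 0 | 31+2 | 42 |
| 27+0 | 31+0 | 7 | 32+2 | 35 |
| 28+0 | 32+0 | 14 | 33+2 | 28 |
| 29+0 | 33+0 | 21 | 34+2 | 21 |
| 30+0 | 34+0 | 28 | 35+2 | 14 |
| 30+4 | 34+4 | 28 | 35+6 | 10 |
| 30+5 | 34+5 | 28 | 36+0 | 9 |
| 30+6 | 34+6 | 28 | 36+1 | 8 |

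aEEG time before entry is above zero for 34 of the 35 GA days and reaches 28 days, about four weekly recordings. The last dosing day reaches 36+0 or later for 2 of 35 GA days. If the day of birth counts as day 1, entry is a day earlier. Then 33 of 35 GA days have aEEG time before entry, and only 30+6 (last dosing day 36+0, 9 days from entry) still overlaps.

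**Effect on aEEG.** Let π be the share of infants already mature at entry, equal in expectation between arms, and δ the mean difference among the others. The observed mean difference is π × 0 + (1 − π) × δ. The documents do not give π. For assumed values of 0.1, 0.3 and 0.5, the difference shrinks to 90%, 70% and 50% of δ.

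**Effect on IVH/PVL and similar yes/no outcomes.** Assume that 10% of each arm has the event before entry, and that new events occur in 10% versus 5% of all randomized infants, none of whom had a prior event.

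- New events only: risk ratio 10/5 = 2.0, risk difference 5 points.
- All events: 20% versus 15%, risk ratio 20/15 = 1.33, risk difference still 5 points.
- Event-free infants only: 10/90 = 11.1% versus 5/90 = 5.6%, difference 5.6 points.
- Standard error of the risk difference with 98 per arm: √((0.10 × 0.90 + 0.05 × 0.95)/98) = 3.7 points for new events, and √((0.20 × 0.80 + 0.15 × 0.85)/98) = 5.4 points for all events.

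Prior events therefore mainly dilute the risk ratio and cost precision. The risk difference hardly moves.

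**The case against.** The strongest reply is that most outcomes are sound and the rest is condensed wording.

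- **It is tempting to infer that no outcome window is tied to entry.** That is wrong. NEC, ROP examinations, hyperglycemia and mortality are dated from enrollment. Brain volume at 40 weeks and anthropometry at 36 weeks always follow entry. Counting from before entry is plain only for aEEG.
- **A reader might infer that harms after 36 weeks go unobserved.** The documents do not support this. Adverse effects are monitored until discharge, NEC runs to discharge, and hospital days cannot be complete at 36 weeks for an infant still in hospital. The 36-week column in Table 1 may be shorthand. What stands is a conflict over which window is analysed.
- **A reader might infer that if half the events predate entry, the risk difference is halved.** The illustration above shows otherwise.
- **The course overlap might be read as undermining the primary outcome.** It touches at most 2 of 35 GA days, the 36-week date applies to both arms alike, and an assessment later in the 36th week could fall after the last dose.
- **aEEG might in practice start only at enrollment.** The text does not say so. Even then, an infant mature at the first recording had reached maturity before treatment, so a baseline rule is still needed.
- **Censoring rules are often left to the analysis plan.** That is fair, and their absence is not the fault raised here. The outcome definition and the timetable, however, are stated in this document, and they are what need correcting.

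**Conclusion.** The point holds in limited form and should be corrected before analysis.

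- **(a) aEEG: clear.** As defined, the outcome counts maturity reached up to 28 days before the first dose and biases the comparison towards no difference. How far depends on the share mature at entry, which the documents do not give.
- **(b) IVH/PVL, nosocomial infection, gastrointestinal bleeding: start unclear.** IVH/PVL is ambiguous rather than wrong. The cost falls on the risk ratio and on precision.
- **(c) Harm window: a real internal conflict.** Table 1 and Clinical data collection say 36 weeks PMA, which is 8 to 42 days after entry. The NEC definition, hospitalization days and adverse-effect monitoring point to discharge.
- **(d) Course against the 36-week assessment: marginal.** It concerns births at 30+5 and 30+6 only, or 30+6 alone if birth is day 1. These are counts of GA days, not shares of infants, since the documents give no GA distribution.

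The primary comparison is not undermined.

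**What to change.** 1. **aEEG.** Take the last recording before randomization as baseline. Analyse time from randomization to the first mature cycle among infants not mature at entry, with censoring at discharge and an explicit rule for death. Restricting on a pre-randomization status keeps the arms comparable. A t or Mann-Whitney test has no value for an infant who never matures under observation. The rule in Clinical data collection that missing data are disregarded, written about follow-up dropouts, would drop such infants if applied here.
2. **IVH/PVL, infection, bleeding.** Count only events that are new or worsened after randomization, with the last routine ultrasound before entry as the IVH/PVL baseline.
3. **Harm window.** Correct Table 1 and Clinical data collection so that infection, NEC, bleeding, treated ROP and hyperglycemia are analysed from randomization to discharge in all infants.
4. **Course and assessment.** Reconcile the passages on the 10-day course and the 36-week assessment for births at 30+5 and 30+6.

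The cost is table wording, a few CRF fields and an analysis rule. aEEG and ultrasound are already planned, though the article says only that scans are regular, so the baseline scan may not fall on day 28. The price is fewer infants in the aEEG analysis.

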### Statistical analysis

The analyses will be based on the intention-to-treat (ITT) principle in accordance with the Consolidated Standards of Reporting Trials (CONSORT). Statistical analyses will be performed with SAS version 9.2 (SAS Institute, Cary, North Carolina). Data will be presented as the mean ± standard deviation or median and interquartile range depending on their distribution. Categorical data, including the primary outcome, will be analyzed using the chi-square test between two groups. Continuous data will be analyzed using Student’s *t* test or the Mann-Whitney test as appropriate. The effect of HC on the dichotomous outcomes will be assessed by multivariable logistic regression analysis including possible confounders, including birth weight and gestational age. Statistical results will be reported as point estimates and 95% confidence intervals.

Mid-term data analysis will be conducted after inclusion of the first 98 patients. The principal investigator will decide whether any measure should be taken in light of the results. Case report forms (CRFs) will be entered by two independent researchers to ensure accuracy.

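### Weight, length and head circumference at 36 weeks are compared without covariate adjustment, which gives up precision that baseline data could recover at little cost

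*Protocol article*

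**What the plan says.** Under Secondary outcomes, the anthropometric endpoint is "Body length, head circumference, and body weight at 36 weeks of PMA". It is a size at one time point; no z-score, growth velocity or baseline-adjusted form is given.

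The Statistical analysis section names the method: "Continuous data will be analyzed using Student’s *t* test or the Mann-Whitney test as appropriate". Covariates appear in the next sentence, for a different class of outcome: "The effect of HC on the dichotomous outcomes will be assessed by multivariable logistic regression analysis including possible confounders, including birth weight and gestational age".

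On baseline data, Clinical data collection states: "Demographic data will include sex, birth weight, gestational age, 5-min Apgar score, surfactant therapy", followed by further perinatal items. It adds: "During HC treatment, respiratory support, blood sugar, blood pressure, and anthropometric data will be collected". It also says: "Population characteristics will be used to compare outcomes between the two groups", without naming a model. Randomization fixes the starting point: "Eligible patients will be randomized at day 28 after birth in each center". Allocation is stratified by two gestational-age bands within each centre.

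**The concern.** The abstract names effects on growth among the secondary outcomes. Any effect of hydrocortisone on growth can act only after day 28. Size at 36 weeks also carries whatever differences existed by day 28, in a population spanning 26+0 to 30+6 weeks' gestation and any birth weight below 1500 g. An unadjusted test leaves all of that variation in the error term.

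The interpretation of a null result is at stake. A moderate slowing of growth could go undetected, and a non-significant comparison with a wide confidence interval would say little about whether growth was affected. The protocol already accepts adjustment for birth weight and gestational age elsewhere, so leaving the growth outcomes out gives up precision for no stated reason.

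**Working it through.** The protocol gives no SD, detectable difference or power for growth, so there is no growth figure to reproduce. The sample size is used here only as a count of infants.

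**Inputs**
- From Sample size calculation: 98 per group recruited, 81 per group before the dropout allowance, significance level 0.05, power 80%.
- From Participants: gestational age 26+0 to 30+6 weeks.
- From Randomization: start at day 28.
- Assumed: two-sided testing (sidedness is not stated) and the correlation r between the baseline covariate(s) and the 36-week measure (not given, so shown over a range).

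**1. Time from day 28 to 36+0 weeks (252 days PMA)**
- Born at 26+0 (182 days): 252 − (182 + 28) = 42 days.
- Born at 28+6 (202 days): 252 − (202 + 28) = 22 days.
- Born at 29+0 (203 days): 252 − (203 + 28) = 21 days.
- Born at 30+6 (216 days): 252 − (216 + 28) = 8 days.

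For the most mature infants, the outcome is read about a week after randomization.

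**2. Unadjusted detectable difference, in SD units**

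(z0.975 + z0.80) × √(2/n) = (1.960 + 0.842) × √(2/n)
- n = 98: 2.802 × 0.1429 = 0.40 SD
- n = 81: 2.802 × 0.1571 = 0.44 SD

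**3. With ANCOVA on a baseline covariate**

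The residual SD is √(1 − r²) times the raw SD. The detectable difference shrinks by that factor, and the equivalent sample-size multiplier is 1/(1 − r²).

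| r (assumed) | Residual SD | Detectable, n = 98 | Detectable, n = 81 | Multiplier | Power for 0.3 SD, n = 98 |
|---|---|---|---|---|---|
| none | 1.00 | 0.40 | 0.44 | 1.00 | 56% |
| 0.3 | 0.95 | 0.38 | 0.42 | 1.10 | 60% |
| 0.5 | 0.87 | 0.35 | 0.38 | 1.33 | 68% |
| 0.7 | 0.71 | 0.29 | 0.31 | 1.96 | 84% |
| 0.8 | 0.60 | 0.24 | 0.26 | 2.78 | 94% |

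The 0.3 SD effect is illustrative; the protocol names no growth difference of interest.

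**4. Width of the confidence interval**

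With 98 per group, the unadjusted 95% half-width is 1.96 × 0.1429 = 0.28 SD. Adjusted, it is 0.28 × 0.87 = 0.24 at r = 0.5, 0.28 × 0.71 = 0.20 at r = 0.7 and 0.28 × 0.60 = 0.17 at r = 0.8. Chance imbalance in a baseline measure has the same ±0.28 SD range, before any reduction from stratification.

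**5. Why a change score is not equivalent**

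With equal variances at the two times, the SD of a change is √(2(1 − r)) times the raw SD: 1.18 at r = 0.3, 1.00 at 0.5, 0.77 at 0.7 and 0.63 at 0.8. Below r = 0.5 this is worse than the raw value, and at every r shown it exceeds the ANCOVA residual SD.

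**The case against.** The best defence is that nothing here is invalid. Randomization takes place at day 28, in blocks and within gestational-age strata, so earlier differences are balanced in expectation. A chance imbalance that produces a significant result is ordinary type I error, already covered by the test and its interval. That stands. A reader might infer that pre-treatment differences swamp or bias the growth comparison; the design does not support that, and the loss is one of precision.

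A second tempting inference is that the needed baseline is already in hand. This is only partly so. Gestational age, birth weight and sex are named as baseline data. Weight, length and head circumference at day 28 before the first dose are not. Anthropometry is placed during treatment, and although dosing is per kilogram, the protocol does not say which weight is used. The preferred fix therefore needs a small change to data collection.

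Third, the size of the gain rests on an assumed r, which need not be the same for the three measures. At 0.3 or 0.5 the improvement is small to modest. That also stands.

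Fourth, growth is followed at 40 weeks PMA and at four corrected ages to 104 weeks, so the 36-week values are not the only evidence. True, but those later measures fall under the same unadjusted rule for continuous data.

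Fifth, covariate models for secondary outcomes are often left to the SAP. Here, however, the protocol names the test for continuous data and assigns adjustment to another class of outcome. That is a stated choice. The general sentence about population characteristics is not limited to dichotomous outcomes, but it is too vague to count as an adjusted model.

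**Conclusion.** The point holds as a matter of efficiency. The unadjusted 36-week comparison is valid but less precise than it needs to be. With 98 per group it detects about 0.40 SD at 80% power (0.44 SD with 81). Baseline adjustment would bring this to 0.35, 0.29 or 0.24 SD at r of 0.5, 0.7 or 0.8. The gain is material at about 0.7 and above, and modest at 0.5 or below.

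These figures assume two-sided testing, complete 36-week data in the stated group sizes, a linear relation between baseline and outcome, and values of r that the document does not supply. They describe the t test; the Mann-Whitney alternative was not calculated.

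Growth should be described as the protocol describes it, as a secondary outcome. A reader might treat it as a key safety endpoint for a steroid trial, but the document does not give it that status. The point merits a change because the remedy is cheap; it does not affect the primary analysis.

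**What to change.** **Minimum change.** Extend the adjustment in Statistical analysis to the continuous growth outcomes: a linear model for each 36-week measure with treatment, gestational age, birth weight, sex and centre. All of these are already recorded or known from the design, so the cost is a sentence of text.

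**Preferred change.** Specify that the first of the planned anthropometric measurements (weight, length and head circumference) is taken at randomization, before the first dose. Analyse each 36-week measure by ANCOVA on its own baseline value, with gestational age and centre in the model, and report the adjusted difference with its 95% confidence interval. Keep raw means by group as description. Do not replace ANCOVA with a plain change score.

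**Cost.** One timed measurement per infant and a slightly longer analysis section, with no extra enrolment. The model should be fixed before any comparison by group, including the planned mid-term analysis. If infants have already been enrolled without a pre-dose measurement, the minimum change still applies to all of them.

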#### Long-term outcomes after hospital discharge

Neurodevelopmental impairment at 104 weeks corrected age: The Bayley Scales of Infant and Toddler Development, Second Edition (BSID II) will be used in this trial.
Cognitive delay: defined as a cognitive score less than 80.Language delay: defined as a language score less than 80.Cerebral palsy and severity of cerebral palsy using the gross motor function classification system.Hearing loss requiring hearing aids at 104 weeks corrected age.Blindness at 104 weeks corrected age: vision loss with only form or shadow vision or no useful vision.Number of readmissions in the first year since the first discharge home.Weight, length, and head circumference at 40 weeks postmenstrual age and 12, 26, 52, and 104 weeks corrected age.Premature birth-related mortality from enrollment to 104 weeks corrected age.Behavioral problems (child behavior checklist) at 104 weeks corrected age. The scores on the checklist will be compared between groups.

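### Hospitalization days are compared with no rule for in-hospital death; if days are counted to death, the comparison leans towards the arm with more deaths (minor)

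*Protocol article*

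**What the plan says.** The Secondary outcomes section of the protocol article lists "Hospitalization days" with no start, end or rule for death. The Clinical data collection section records the same item among other durations: "invasive ventilator-assisted time, days of hospitalization, days on supplemental oxygen".

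The Statistical analysis section sets the population and the test: "The analyses will be based on the intention-to-treat (ITT) principle", and "Continuous data will be analyzed using Student’s *t* test or the Mann-Whitney test as appropriate".

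Death is dealt with elsewhere, but not for this outcome:
- The primary outcome counts it through a composite: "The primary outcome is survival without moderate or severe BPD at PMA 36 weeks".
- A separate long-term outcome covers a subset of deaths: "Premature birth-related mortality from enrollment to 104 weeks corrected age".
- The missing-data statement, "the missing data will be ignored in the analysis", is made about dropouts during follow-up and does not mention death.

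**The concern.** A hospital stay can end in two opposite ways: discharge alive, or death. Fewer days is a good result only in the first case. A two-sample test on the raw count cannot tell them apart. An infant who dies on day 45 would contribute 45 days and would rank better than a survivor who goes home on day 80. In the primary outcome the same infant is a failure.

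If mortality differs between the arms and deaths come before the infants would have gone home, the arm with more deaths shows a shorter stay with no true effect on stay. The direction is awkward for a trial that sets out to establish safety as well as efficacy.

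**Working it through.** **Which reading the text supports.** Under intention to treat all randomized infants stay in the analysis. An infant who dies in hospital has a count of hospital days, so the value is not missing, and the statement about dropouts does not remove it. A survivors-only analysis is stated nowhere and would select on an event after randomization. Counting days to death is therefore the natural reading, but it is an inference.

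**Inputs.** The article gives no figure for length of stay, so there is none of its own to reproduce.
- From the article: 98 infants per arm (Sample size calculation).
- Assumed: survivors' stay has mean 80 days and SD 20; deaths fall uniformly between day 30 and day 60 (mean 45); HC has no effect on survivors' stay; mortality is 3% vs 1%, 6% vs 2%, or 10% vs 4%.

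**Shift in the mean.** Each death replaces an expected 80 days by 45, so the shift is (difference in mortality) × (80 − 45). The standard error of the difference in means is 20 × √(2/98) = 2.86 days.

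| Deaths | Shift (days) | Shift / SE |
|---|---|---|
| 3% vs 1% | 0.02 × 35 = 0.7 | 0.24 |
| 6% vs 2% | 0.04 × 35 = 1.4 | 0.49 |
| 10% vs 4% | 0.06 × 35 = 2.1 | 0.73 |

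**Shift in the Mann-Whitney probability.** This is the chance that an infant in the lower-mortality arm has the longer stay. With no effect on stay it should be 0.5. Simulation of 4000 trials per scenario gave 0.509, 0.517 and 0.528, with a standard error of 0.042. The artefact is the distance from 0.5:
- 0.009 / 0.042 = 0.2 SE
- 0.017 / 0.042 = 0.4 SE
- 0.028 / 0.042 = 0.7 SE

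A direct formula agrees: 0.5 + (difference in mortality) × (q − 0.5), where q is the chance that a survivor's stay exceeds a dead infant's count. Averaging the normal probability Φ((80 − x)/20) over x from 30 to 60 gives q = 0.946, hence 0.509, 0.518 and 0.527.

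**Second set of assumptions.** Here stay is counted from randomization (gamma, mean 50, SD 20), death is uniform over the stay the infant would have had, and there is no effect on stay. There were 3000 runs per scenario with 98 per arm. The last two columns give the rate of a false significant finding of shorter stay on HC, nominally 2.5%.

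| Deaths, control vs HC | Mean difference, HC − control (days) | t test | Mann-Whitney |
|---|---|---|---|
| 2% vs 2% | −0.1 | 3.1% | 2.6% |
| 2% vs 5% | −0.8 | 4.8% | 3.9% |
| 2% vs 10% | −1.9 | 10.0% | 8.7% |
| 5% vs 15% | −2.5 | 12.1% | 11.4% |

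On average a death loses half of 50 days, so the expected differences are 25 × 0, 0.03, 0.08 and 0.10, that is 0, 0.75, 2.0 and 2.5 days. The simulated values agree with these. With deaths ranked worst, the Mann-Whitney false-favourable rate falls to 2.3%, 1.5%, 0.2% and 0.1%. The last two rows need an excess of 8 and 10 percentage points in deaths, for which the article gives no basis.

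**The case against.** The strongest objection is that the article is silent and states no error. Survivors-only, days to death and worst rank all fit its words, and how deaths enter a secondary duration is often left to a full protocol or analysis plan that is not shown here. Mann-Whitney is already allowed, and giving deaths the worst rank is only a scoring convention within it. It is therefore fair to say that the treatment of deaths is inferred and that the point is small. The point still stands because the article does fix the outcome, the population and the test, and that combination taken as written lets a stay cut short by death count as short.

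Several stronger readings are tempting, and the documents do not support them:
- *That the plan scores death as a favourable stay.* It does not say so. A death after a long stay would not score as short either.
- *That the bias is 0.5 to 1.4 standard errors, with the direction reversed.* Those figures are the gap between raw scoring and worst-rank scoring, for example 0.509 against 0.489. These are two different estimands, and worst rank moves away from 0.5 because it counts the mortality difference. The artefact is the smaller figure worked out above.
- *That the trial expects HC to improve survival, so a benefit would be hidden.* The Sample size calculation and the Discussion posit a reduction in moderate or severe BPD. No mortality effect is assumed.
- *That a harm would pass as a benefit.* Deaths also count in the primary outcome, appear in part in the long-term mortality outcome, and are listed as serious adverse reactions under the academic board. Nobody would judge mortality from length of stay alone.
- *That oxygen, CPAP and ventilator days have the same defect.* They are collected but are not listed as outcomes.

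**Conclusion.** The concern holds in a conditional form and is minor. If days are counted to death, as the plain count and intention to treat imply, and if deaths come before expected discharge, the comparison of hospitalization days is biased towards the arm with more deaths.

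The artefact is about 0.7 to 2.1 days, roughly 0.2 to 0.7 standard errors, for assumed deaths of 3% vs 1% to 10% vs 4%. With equal mortality it is near zero. Every input except the 98 per arm is an assumption, because the article gives neither mortality after day 28 nor the distribution of stay. The primary outcome is not affected.

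**What to change.** State in the Statistical analysis section that hospitalization days will be compared by the Mann-Whitney test with in-hospital deaths given the worst rank. Alternatively, analyse time from randomization to discharge alive by cumulative incidence with death as a competing event, neither censored nor counted as discharge. Report all in-hospital deaths by arm beside the result, because the listed mortality outcome is limited to deaths related to premature birth. Show stay among survivors as a descriptive line only.

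The text cost is a sentence or two, best added before unblinding. The analysis needs the length of each stay and whether it ended in discharge alive or in death. The article lists days of hospitalization but not dates of discharge or death, so the case report form should be checked for these. The downside is that a worst-rank result is less direct to read than a mean difference in days.
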